## Abstract

**Background:**

Bariatric surgery is currently the most effective form of obesity management for those whose BMI is greater than 40 (or 35 with co morbidities). A minority of patients, however, either do not show the desired loss of excess weight or show weight regain by follow up. Research highlights some of the reasons for this variability, most of which centres on the absence of any psychological support with patients describing how although surgery fixes their body, psychological issues relating to dietary control, self esteem, coping and emotional eating remain neglected.

The present study aims to evaluate the impact of a health psychology led bariatric rehabilitation service (BRS) on patient health outcomes. The bariatric rehabilitation service will provide information, support and mentoring pre and post surgery and will address psychological issues such as dietary control, self esteem, coping and emotional eating. The package reflects the rehabilitation services now common place for patients post heart attack and stroke which have been shown to improve patient health outcomes.

**Methods/Design:**

The study is a randomised control trial and patients will be allocated to receive either usual care or the bariatric rehabilitation service pre and post bariatric surgery. Follow up measures of weight loss and psychological issues will be taken at baseline (2 weeks preoperatively), 3, 6 and 12 months postoperatively. The contents of the bariatric service and the follow up measures are based on previous pilot work and have been developed further by the research team working closely with two patient support groups (BOSPA & WLSinfo). This study will take place in St Richard's Hospital in Chichester in the UK.

**Discussion:**

It is predicted that a bariatric rehabilitation service will improve weight loss following surgery and will also facilitate changes in other psychological variables such as quality of life, dietary control, self esteem, coping and emotional eating. This also has cost implications for the NHS and other healthcare providers as improved effectiveness of bariatric surgery reduces the health costs of obese patients in the longer term.

**Trial registration:**

ClinicalTrials.gov NCT01264120.

## Background

Obesity is caused by people consuming more energy than they expend and is associated with reduced life expectancy and many serious conditions including heart disease, stroke, diabetes, cancer, gallstones, fatty liver disease and sleep apnoea [1]. Currently almost two-thirds of UK adults are either overweight or obese with overall costs to society forecast to reach £50 billion per year by 2050 on current trends [2].

Although the most common form of management emphasizes changes in diet and exercise, research indicates that weight loss surgery (wls) is the most effective intervention for weight loss for those whose BMI is greater than 40 (or 35 for those with significant health problems) [3]. A systematic review of wls [4] concluded that the mean percentage excess weight loss (EWL) for the Roux-en-Y gastric bypass was 67% and for the gastric band was 42% at one year. WLS has also been shown to result in improvements in a number of other patient outcomes including quality of life, mood, subjective health status and perceptions of eating control [5,6]. Weight loss outcomes are not consistent for all patients and a large minority of patients either do not show the desired loss of excess weight or regain weight by follow up.

Previous qualitative and quantitative research by the principal investigator has explored the mechanisms involved in successful and failed bariatric surgery to highlight how effectiveness could be improved [6-8]. The results indicated that successful surgery is associated with a reduction in hunger and preoccupation with food and a sense of being more in control of food intake. In contrast, less successful surgery was associated with feeling unprepared for the changes required after surgery, reporting being unsupported in the time following surgery and a sense that although surgery fixes their body, psychological issues relating to dietary control, self esteem, coping and emotional eating remain neglected. This highlights key areas that need to be addressed to improve patient outcomes following surgery. It also confirms the conclusions made by Saltzman et al. [9] who conducted a review of articles related to weight loss surgery and indicated that such patients require multidisciplinary care including psychological input. Furthermore, NICE guidelines [10] state that surgery for obesity should be undertaken only by a multidisciplinary team that can provide psychological support before and after surgery. This is currently missing in the current standard package of care in many centres including for patients at Chichester.

The present study therefore aims to evaluate a health psychology led bariatric rehabilitation service to explore the impact on patient health outcomes following surgery. The bariatric rehabilitation service will offer information, support and mentoring pre and post surgery and finds reflection in the rehabilitation services which are now common place for patients post heart attack and stroke [11]. In particular, research indicates that rehabilitation for other conditions can improve a number of patient outcomes such as return to work, quality of life and health related behaviours [12]. In a similar vein it is predicted that a bariatric rehabilitation service would primarily improve weight loss following surgery but would also facilitate changes in other psychological variables such as dietary control, self esteem, coping and emotional eating.

## Methods/Design

### Study design

The study will involve a trial (open randomised parallel group control trial) with patients allocated to receive either usual care or the bariatric rehabilitation service (BRS) pre and post bariatric (obesity) surgery. Follow up measures will be recorded at 3, 6 and 12 months post-surgery at routine follow-up clinics or by post. In addition, qualitative interviews will be carried out with 20 participants from both arms of the trial (BRS n = 10; usual care n = 10). This study received a favourable ethical opinion from the Kent Research Ethics Committee, National Research Ethics Service.

### Development of the intervention

The content of the BRS and the follow up measures are based on previous qualitative research and pilot work exploring what bariatric patients want and why bariatric surgery either fails or succeeds from the patients' perspective [6-8]. Furthermore, pilot research has explored the impact of bariatric surgery on changes in mood, cognitions and eating behaviours. The quantitative measures and qualitative responses derived from these studies formed the basis of the intervention and the measures for the present study.

### Participants and recruitment

St Richard's Hospital in Chichester, West Sussex, UK, offers a NHS based bariatric service for obese patients with a BMI over 40 (or 35 with serious co morbidities). This is the largest centre in the UK, with approximately 500 patients per year receiving a bariatric operation at this clinic (70% being a primary bypass and 20% bands (the remaining 10% are revisions)). Patients will be recruited if they have been approved for surgery and had their date set for their operation.

Patients will be included if they consent, are aged 18 or over, have attended the bariatric clinic at Chichester, been accepted for surgery and have funding in place (i.e. the PCT has agreed to pay for their surgery). Recruitment will take place over a 12 month period. Those who cannot effectively read or speak English will be excluded as this would pose a difficulty for implementing the intervention and for data collection.

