### Sample size and power calculation

Petrie et al [12] carried out an intervention (34 controls and 31 in the intervention group) with patients post MI which involved the addition of a health psychologist to usual care who focused on a number of psychological factors including beliefs, expectations and behaviour. The results from this study showed that this intervention produced a significant improvement in a certain patient outcome by follow up of about 20% with a standard error of 40%. Based on the information from this study, were the study to be repeated, 85 subjects in each arm would be needed for 90% power for the effect of the intervention on this patient outcome at a two-sided significance level of 0.05. It can be argued that this can be used as the basis for considering the expected improvement for the present study. Buchwald et al [13] reported that the mean percentage of excess weight loss among obese patients offered bariatric surgery was 62%. If the psychological intervention described here improved this weight loss by a further 20% (i.e. to 74%), by the above reasoning, at 0.05 significance 85 patients randomised to each group would give 90% power to demonstrate statistical significance of the intervention. Bands are expected to constitute 20% of all presenting patients. If 90% power is required to find the intervention statistically significant for bands and for bypass, separately, then 85 patients will need to be randomised for each of bands and bypass for each arm of the study. However we hypothesise that bands will be more responsive to the intervention than bypass and hence we will aim for 60 bands and 85 bypass patients in each of the two arms of the study, making a total of 290 patients for the study. Allowing for some attrition and refusals we propose to invite 335 patients to be recruited into the study, ensuring that 180 of these are bands and the remainder bypass. This sample size will enable us to detect a 20% improvement on usual care in the entire sample with power in excess of 90% and will also enable us to carry out some sub group analyses to explore differential effects with 90% power within those patients who receive either a gastric band or a gastric bypass.

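### The stated centre volume supplies about 100 band patients in 12 months, so the target of 120 randomised bands and its 90% subgroup power cannot be met as written

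*Protocol article*

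**What the plan says.** All from the protocol article.

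- **One site** (Abstract, Methods/Design): "This study will take place in St Richard's Hospital in Chichester in the UK".
- **Volume and mix** (Participants and recruitment; revisions account for the last tenth): "approximately 500 patients per year receiving a bariatric operation at this clinic (70% being a primary bypass and 20% bands".
- **Period** (same section): "Recruitment will take place over a 12 month period".
- **Expected mix** (Sample size and power calculation): "Bands are expected to constitute 20% of all presenting patients".
- **Randomisation target** (same section), 290 patients in all: "we will aim for 60 bands and 85 bypass patients in each of the two arms of the study".
- **Invitations** (same section): 335 patients, "ensuring that 180 of these are bands and the remainder bypass". No refusal or attrition rate is given.
- **Power** (same section): over 90% for the whole sample, and 90% within the band and bypass groups taken separately.

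Under Procedure, consent and allocation take place at the pre-operative visit two weeks before surgery.

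**The concern.** The volume, the procedure mix, the recruitment period and the procedure quotas are all printed, and they do not fit together. Because patients are randomised two weeks before their operation, the number of band operations in the period caps the number of band patients who can be randomised. That cap lies below the target before any loss to refusal, missing funding or the English-language exclusion.

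At stake is the band subgroup analysis, for which the plan claims 90% power. If nothing changes, recruitment overruns its stated period, or the band quota is altered during the trial, or a band result is reported from fewer patients than its power statement assumes. The conflict can be seen before the first patient is enrolled and cannot be repaired once recruitment has closed.

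**Working it through.** **1. The plan's own figures.** The inputs are a difference of 20, a spread of 40, two-sided alpha 0.05 and 90% power. The document calls the 40 a standard error; its sample size follows only if it is read as an SD, so the effect is 20/40 = 0.5 SD. Then n per arm = 2 × (1.960 + 1.282)² / 0.5² = 84.06, rounded up to 85, which matches. The total 2 × (60 + 85) = 290 also matches.

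**2. Supply against target.**
- Bands available in 12 months: 500 × 0.20 = 100.
- Bands to be randomised: 2 × 60 = 120, a shortfall of 20.
- Time to randomise 120 with every band patient taking part: 120/100 × 12 = 14.4 months.
- Bands to be invited: 180, a shortfall of 80 if invitations fall in the same 12 months. At 100 a year they would take 180/100 × 12 = 21.6 months.
- Annual volume needed at a 20% share: 120/0.20 = 600 operations for the first figure, 180/0.20 = 900 for the second.

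**3. The invitation split.** 335 − 180 = 155 bypass invitations, against 2 × 85 = 170 bypass patients to be randomised. That fails even with no refusals. Bypass supply is not the limit: 500 × 0.70 = 350 a year.

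**4. Yield.** The plan states no rate. Its band figures imply 120/180 = 67%; its overall figures imply 290/335 = 87%. At 67%, 100 bands give about 67 randomised, or 33 per arm.

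**5. Band power.** Two-sided two-sample t test, alpha 0.05. The normal approximation, Φ(d × √(n/2) − 1.960), agrees to within about one percentage point. The second column assumes an effect for which 60 per arm gives 90% power, about 0.6 SD; the plan states no such figure.

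| Bands per arm | Basis | 0.5 SD | about 0.6 SD (assumed) |
|---|---|---|---|
| 60 | planned | 78% | 90% |
| 50 | every band patient in 12 months | 70% | 84% |
| 33 | 67% yield | 52% | 67% |

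Example for 50 per arm at 0.5 SD: 0.5 × √25 − 1.960 = 0.540, and Φ(0.540) = 0.705; the t test gives 0.697.

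**6. Pooled comparison.** At 145 per arm and 0.5 SD, power is about 99%. By the plan's own calculation 85 per arm already gives 90%.

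**The case against.** **The figures are approximate.** The centre's volume is given as approximate, and the 20% might be a share of something other than all operations. Taken as a share of primary operations only, the supply is 500 × 20/90 = 111, still under 120. Volume would have to be 20% above the stated figure, with full participation, to reach 120. Revisions are a partial escape: if all of the roughly 50 a year were band procedures, supply would be 150, above 120 but below 180. The document lists revisions separately from bands and says nothing of the kind.

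**The invitations are not tied to 12 months.** This stands. The article attaches no period to the 335 invitations, and information sheets are handed out on acceptance for surgery, so invitations need not match operations in the same year. The 21.6 months is therefore conditional. The conflict of 100 with 120 does not depend on it.

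**Bands are expected to respond more.** The plan gives this as its reason for 60 rather than 85, so showing 0.5 SD alone would be one-sided. Even with an effect large enough to make 60 per arm sufficient, 50 per arm gives about 84%. To reach 90% with 50 per arm the effect must be about 0.65 SD, a difference of about 26 in the plan's units instead of 20.

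**The main comparison is safe.** This also stands, and it limits the weight of the point. A reader might infer that the whole trial is underpowered or must stall. The documents do not support that, because bypass patients can make up the number.

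**Conclusion.** The point holds for the band target. On the document's own figures about 100 band patients come through in 12 months against 120 to be randomised, and nothing in the article (second site, longer period, rising band volume) closes the gap. The stated band sample size and its 90% power are wrong as written.

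The drop from 90% to 70% might be put down entirely to recruitment. That would be mistaken: at 0.5 SD the planned 60 per arm already gives only about 78%, so the supply ceiling costs about 8 points and the rest was there before. Nor does the 13% gap between 335 and 290 serve as the plan's allowance for band refusals, since its band figures imply 33%. Any band forecast below the ceiling of 100 is therefore an assumption.

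The power figures rest on reading 40% as an SD and on carrying that effect over to weight loss, as the plan does. The defect is confined to a subgroup and to the invitation quota. It should be corrected before recruitment, but it does not endanger the pooled result.

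**What to change.** Reconcile Participants and recruitment with Sample size and power calculation in one of two ways.

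1. **Keep 12 months.** Set the band number at what the period can supply: no more than about 100, less refusals. Fill the remaining places to 290 from the roughly 350 bypass patients a year. Replace the 90% band power with the recomputed range (at 0.5 SD, about 52% at 33 per arm to 70% at 50 per arm; about 84% at 50 per arm if the stronger band effect is assumed and stated), and label the band analysis exploratory.
2. **Keep 120 bands.** Lengthen the stated recruitment period: at least 14.4 months, and 120/67 × 12, about 21.6 months, at the 67% yield. Restate band power here too, since 60 per arm gives 90% only under a larger effect than the one stated.

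In either case correct the 180/155 invitation split and state the refusal rate behind it. If 67% applied to both procedures, 290 randomised would need 290/0.667 = 435 invitations, just within the roughly 450 band and primary bypass patients a year.

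The first option costs a less favourable band power figure and some of the deliberate oversampling of bands; the second costs time. The pooled comparison keeps its stated power above 90% under both.

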### Randomisation

All patients who fulfil the inclusion criteria will be given an information sheet. They will be given several weeks to read the information and then they will be approached by the researcher, asked if they have any questions regarding the information sheet and if interested offered a written consent form. Once a patient has consented the researcher will reference the third party blinded randomization, which will be provided by the clinical trial unit at Surrey University, to indicate whether they are allocated to either the BRS or usual care.

### Sample size and power calculation

Petrie et al [12] carried out an intervention (34 controls and 31 in the intervention group) with patients post MI which involved the addition of a health psychologist to usual care who focused on a number of psychological factors including beliefs, expectations and behaviour. The results from this study showed that this intervention produced a significant improvement in a certain patient outcome by follow up of about 20% with a standard error of 40%. Based on the information from this study, were the study to be repeated, 85 subjects in each arm would be needed for 90% power for the effect of the intervention on this patient outcome at a two-sided significance level of 0.05. It can be argued that this can be used as the basis for considering the expected improvement for the present study. Buchwald et al [13] reported that the mean percentage of excess weight loss among obese patients offered bariatric surgery was 62%. If the psychological intervention described here improved this weight loss by a further 20% (i.e. to 74%), by the above reasoning, at 0.05 significance 85 patients randomised to each group would give 90% power to demonstrate statistical significance of the intervention. Bands are expected to constitute 20% of all presenting patients. If 90% power is required to find the intervention statistically significant for bands and for bypass, separately, then 85 patients will need to be randomised for each of bands and bypass for each arm of the study. However we hypothesise that bands will be more responsive to the intervention than bypass and hence we will aim for 60 bands and 85 bypass patients in each of the two arms of the study, making a total of 290 patients for the study. Allowing for some attrition and refusals we propose to invite 335 patients to be recruited into the study, ensuring that 180 of these are bands and the remainder bypass. This sample size will enable us to detect a 20% improvement on usual care in the entire sample with power in excess of 90% and will also enable us to carry out some sub group analyses to explore differential effects with 90% power within those patients who receive either a gastric band or a gastric bypass.

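### The 85 per arm gives 90% power for excess weight loss only at an unstated SD of about 24 to 25 points, and 60 bands per arm fall short of 90% at the plan's own effect size

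*Protocol article*

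**What the plan says.** All of this is in the Protocol article, Sample size and power calculation.

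- The starting point is a trial of a health psychologist added to usual care after MI, with "34 controls and 31 in the intervention group". It is reported to have shown "a significant improvement in a certain patient outcome by follow up of about 20% with a standard error of 40" per cent. The outcome is not named.
- From this the article concludes that "85 subjects in each arm would be needed for 90% power for the effect of the intervention", "at a two-sided significance level of 0.05".
- It then turns to weight loss. A cited review is said to show that "the mean percentage of excess weight loss among obese patients offered bariatric surgery was 62" per cent. The text continues: "If the psychological intervention described here improved this weight loss by a further 20% (i.e. to 74%), by the above reasoning", and 85 per arm is again said to give 90% power.
- It notes that 90% power within bands and within bypass separately would take 85 of each in each arm. It then plans 60 bands and 85 bypass per arm (145 per arm, 290 in all), because band patients are expected to benefit more. No size is given for that larger benefit.
- It closes by claiming more than 90% power for a 20% improvement in the whole sample, and 90% power within each procedure.

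No standard deviation of %EWL appears anywhere in the article.

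**The concern.** Power for a comparison of means depends on the difference divided by the SD of the same outcome. The article has a difference and a spread for one outcome (post-MI) and a difference, but no spread, for another (%EWL). It takes the sample size from the first and applies it to the second. That is valid only if the standardised effect is the same, which requires a particular SD of %EWL that is neither stated nor supported.

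Two further details do not fit. The spread is labelled a standard error, which cannot be right given the rest of the sentence. And bands are cut from 85 to 60 per arm while the 90% claim within bands is kept.

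At stake are the 90% claims for bypass and bands, the claim of more than 90% overall, and so the justification for 290 patients.

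**Working it through.** **Inputs.** Two-sided 0.05 (z = 1.960) and 90% power (z = 1.2816); effect 20 and spread 40 in the post-MI trial, with 34 and 31 patients; control %EWL 62 and target 74; planned 60 bands, 85 bypass and 145 in total per arm. All come from the sample size section.

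**1. Reproducing 85.** For two means, n per arm = 2 × (1.960 + 1.2816)² × (SD/difference)². With 20 and 40: 2 × 10.507 × 4 = 84.06, rounded up to **85**. The match is exact. The t-test version gives 90.0% power at 85. Alternatives do not give 85: one-sided testing gives 69, and comparing proportions of 0.62 and 0.74 gives 316. So the figure rests on a standardised difference of 0.5, with the 40 used as an SD.

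**2. The label.**
- If 40 were the standard error of a difference of 20, z = 20/40 = 0.5 and p = 0.62. The same sentence calls the effect significant.
- If 40 is an SD, the standard error is 40 × √(1/34 + 1/31) = 9.93, t = 20/9.93 = 2.01 and p = 0.048.

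Only the SD reading fits both the significance claim and the 85.

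**3. Transfer to %EWL.** The target is 74 − 62 = 12 points as printed, or 62 × 0.20 = 12.4 unrounded. The SD that gives 90% power at n per arm is difference / [3.2415 × √(2/n)]:

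| n per arm | SD for 12 points | SD for 12.4 points |
|---|---|---|
| 60 | 20.3 | 21.0 |
| 85 | 24.1 | 24.9 |
| 145 | 31.5 | 32.6 |

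The 85 therefore needs an SD of about 24 to 25 points. The whole-sample claim tolerates an SD up to about 31 for 12 points.

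**4. Two readings of the 40%.**
- *Relative to the mean:* SD = 0.40 × 62 = 24.8, difference 12.4, ratio 0.5, n = 85. The article's figure follows.
- *EWL points:* 12/40 = 0.30 gives n = 234; 12.4/40 = 0.31 gives n = 219.

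**5. Power over an assumed range of SD.** Power = Φ[difference / (SD × √(2/n)) − 1.96]. Figures are for 12 points, with 12.4 points in brackets. The SD values are assumptions, because the article gives none.

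| SD | n per arm for 90% | Power at 60 | Power at 85 | Power at 145 |
|---|---|---|---|---|
| 20 | 59 (55) | 91% (92%) | 98% (98%) | >99% |
| 25 | 92 (86) | 75% (78%) | 88% (90%) | 98% (99%) |
| 30 | 132 (124) | 59% (62%) | 74% (77%) | 93% (94%) |
| 35 | 179 (168) | 47% (49%) | 61% (64%) | 83% (86%) |
| 40 | 234 (219) | 38% (40%) | 50% (52%) | 72% (75%) |

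The t-test version at SD 40 and 12 points gives 49% at 85 per arm and 72% at 145.

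**6. Bands at the plan's own effect.** With 0.5 SD and 60 per arm: 0.5/√(2/60) = 2.739; 2.739 − 1.960 = 0.779; power = **78%**. For 90% the standardised effect must be 3.2415 × √(2/60) = 0.59, or about 0.60 with the t-test. If the 40% is relative, that is 0.592 × 40 = 23.7, a relative gain of about 24% rather than 20%.

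**The case against.** The strongest reply is that 85 is not shown to be wrong. The article states the gain as relative and spells out the resulting target. If the 40% is read on the same relative scale, the ratio stays at 0.5 and 85 follows exactly. This stands. A reader might infer that a 20% relative gain was mistaken for 20 percentage points; the text does not establish that. A reader might also infer that the trial needs 219 to 234 per arm. That requires the 40 to be in EWL points, which the article never says, and an SD of 20 would leave the trial well powered. What survives is that the SD of %EWL needed for the claim is neither stated nor supported.

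A second tempting inference comes from the Background, which reports that mean %EWL for bypass "was 67% and for the gastric band was 42% at one year". A reader might take 20% of 42 = 8.4 points for bands, set it against an SD of 24.8, and conclude that band power is far below 78%. That rescales the mean but not the SD. On the same relative rule the band SD is 0.40 × 42 = 16.8 and the ratio returns to 0.5.

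Third, the article does not assume only 0.5 SD in bands; it expects a larger response. That is fair, but with no size attached it cannot support a stated 90%.

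Fourth, the standard error label is wording and changes no result. That is true, but as printed it contradicts its own sentence and gives a reader the wrong quantity to check.

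Finally, borrowing an effect from post-MI rehabilitation is presented openly as arguable. It is a judgement the authors may make, and this point does not ask them to abandon it.

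**Conclusion.** The point holds as an unsupported input and a mislabelled one, not as proof that the sample size is wrong.

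- The 90% claim at 85 per arm holds for 62% to 74% only if the SD of %EWL is about 24 to 25 points. If the 40 means EWL points, power is about 49 to 52% at 85 per arm and 72 to 75% at 145. No correct sample size can be named without an SD for %EWL.
- The printed standard error must be a standard deviation. This follows from the article's own figures.
- At the plan's own 0.5 SD, 60 bands per arm give 78% power. The stated 90% needs about 0.60 SD, and the larger band effect is not quantified. This holds whichever way the 40% is read.
- The whole-sample claim is the most robust. At 145 per arm it holds for 12 points up to an SD of about 31.

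These results assume an unadjusted comparison of two means with equal arms and the planned numbers analysed in full.

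**What to change.** In the sample size section:

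1. Replace *standard error* by *standard deviation* for the 40%, and say whether the 20% and 40% are relative or in points.
2. State the target difference in %EWL points and the assumed SD of %EWL with its source, using the centre's own follow-up data if available.
3. Restate power at 145, 85 and 60 per arm in a short table over a range of SD, for example 20 to 40 points.
4. For bands, either give the size of the larger effect assumed (about 0.60 SD is needed for 90% at 60 per arm) or restate band power as about 78% at 0.5 SD.

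The cost is a recalculation, a source for one SD and one rewritten paragraph. The downside is that the stated power may become less favourable, most likely for the separate band and bypass analyses.

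### The 90% power claimed within each procedure group is not delivered: 85 per arm contains no loss allowance, bypass has fewer invitations than its target, and 60 bands per arm needs an unstated larger effect

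*Protocol article*

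**What the plan says.** All of this stands in the section Sample size and power calculation of the protocol article.

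- The effect is borrowed from a psychological intervention after myocardial infarction, described as an "improvement in a certain patient outcome by follow up of about 20% with a standard error of 40" per cent. From this the section derives that "85 subjects in each arm would be needed for 90% power" "at a two-sided significance level of 0.05".
- This is transferred to excess weight loss, with a baseline of 62% "improved this weight loss by a further 20% (i.e. to 74"%), and the number is tied to randomisation: "85 patients randomised to each group would give 90% power to demonstrate statistical significance of the intervention".
- For the same power in each procedure group, "85 patients will need to be randomised for each of bands and bypass for each arm of the study".
- The targets actually adopted are 60 bands and 85 bypass per arm, 290 in total. The band number is reduced because a larger response is expected in bands; its size is not given.
- "Allowing for some attrition and refusals we propose to invite 335 patients to be recruited into the study", of whom 180 are to be bands and the rest bypass.
- The section closes by claiming more than 90% power in the whole sample and 90% power within band and within bypass patients.

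**The concern.** A power calculation gives the number of patients who must contribute an outcome. If that number is used as the number randomised and some patients are then lost, the power at analysis is lower than stated. Here the plan expects losses but gives no rate for them. It also combines them with refusals, which are a different thing: a refusal happens before randomisation and costs an invitation, whereas a loss after randomisation costs power.

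Whether the single allowance is enough has to be judged separately in each procedure group, because the 90% claim is made separately in each. What is at stake is how a null result within bands or within bypass would be read. With a stated power of 90% it would look more conclusive than the numbers justify.

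**Working it through.** **Inputs.** From the sample size section: effect 20, spread 40, two-sided alpha 0.05, power 90%; targets of 85 bypass and 60 bands per arm (170 and 120 over two arms, 290 in total); 335 invited, 180 of them bands. The 40 is called a standard error, but 85 is reproduced only if it is used as an SD, so the standardised effect is d = 20/40 = 0.5. Loss rates of 5%, 10% and 20% are assumptions; the article gives none.

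**1. The plan's own 85.** Normal approximation: n = 2 × (1.960 + 1.282)² × (40/20)² = 84.06 per arm, rounded up to 85. The t-test gives 85.03, and power at 85 is 89.99%. So 85 is an analysed number with no slack. The powers below are t-test powers at d = 0.5; the normal approximation is up to about 0.7 of a percentage point higher.

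**2. The pooled allowance.** 335 − 290 = 45, and 45/335 = 13.4% for refusals and later losses together.

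**3. The allowance by procedure.**

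| | Invited | Target (two arms) | Margin |
|---|---|---|---|
| Bands | 180 | 2 × 60 = 120 | +60 (33% of those invited) |
| Bypass | 335 − 180 = 155 | 2 × 85 = 170 | −15 |

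The whole margin lies with bands. Bypass has less than none.

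**4. Bypass power.** At best 155/2 = 77.5 per arm.

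| Loss after randomisation (no refusals) | Analysed per arm | Power |
|---|---|---|
| 0% | 77.5 | 87.1% |
| 5% | 77.5 × 0.95 = 73.6 | 85.4% |
| 10% | 77.5 × 0.90 = 69.75 | 83.5% |

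Any refusal lowers these further. Even if the split were repaired so that 85 bypass patients per arm were randomised, a 10% loss would leave 76.5 per arm and 86.7% power.

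**5. Band power.** At the target of 60 per arm analysed, power is 77.5% (78.2% by the normal approximation). For 90% with 60 per arm the effect must be (1.960 + 1.282) × 40 × √(2/60) = 23.7 by the normal approximation, or about 23.9 by the t-test: about 24 instead of 20 at an SD of 40. The section expects bands to respond more but states no such figure.

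**6. Whole sample.** With 60 + 85 = 145 randomised per arm and 20% loss, 145 × 0.80 = 116 per arm are analysed and power is about 97%.

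**The case against.** The strongest reply is that the plan does allow for attrition: it raises 290 to 335 for that purpose. The 290 is described as an aim and is not itself called the number randomised, so it can fairly be read as the number wanted after losses. This stands. A reader might infer that the 90% fails simply because 85 is the no-loss number; that does not follow on its own, since the inflation to 335 might have covered it. What defeats the reply for bypass is the split, which leaves 155 invitations for a target of 170 under either reading.

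For bands the reply is stronger. With 180 invited for 120, losses and refusals of up to a third still leave 60 per arm. If all 180 were randomised there would be 90 per arm, and up to 1 − 85/90 = 5.6% loss would still leave 85. It would therefore be wrong to blame attrition for the band shortfall; it comes from choosing 60 per arm without stating the effect that justifies it.

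Two further inferences go beyond the text. The power is not tied to the 12-month visit: the sample size section names no time point, and Primary outcome measures lists 3, 6 and 12 months. Nor is there a rule that recruitment stops once 335 have been invited.

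It can also be said that the subgroup analyses are exploratory and that a condensed article may leave loss rates to the full protocol. That is fair as far as the missing rates go. It does not cover the 90% claim and the 180/335 split, which the article states itself and which disagree.

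**Conclusion.** The within-procedure claim of 90% power does not hold on the plan's own numbers. For bypass it is at most about 87% before any refusal or loss, and about 85% and 83% at an assumed 5% and 10% loss. For bands at the target of 60 per arm it is about 78% at the stated effect; 90% would need an effect of about 24 rather than 20.

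The shortfall in bypass rests on the invitation split, which any attrition makes worse. Calling 85 the number randomised is a wording fault that would cost a few points more even with the split repaired. The claim of more than 90% power in the whole sample is not affected.

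These figures assume that the 40% is an SD, that the standardised effect of 0.5 carries over to excess weight loss as the plan argues, equal allocation, and an unadjusted two-sample comparison. The loss rates are illustrative, but the bypass ceiling of about 87% does not depend on them.

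**What to change.** In Sample size and power calculation:

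1. State 85 bypass and 60 bands per arm, and the total of 290, as patients analysed.
2. Give the expected refusal rate and the expected loss after randomisation as two separate rates.
3. Make the band/bypass split of the 335 invitations agree with targets of 120 bands and 170 bypass plus those losses.
4. Replace the within-procedure 90% by the power that each group reaches after the expected loss (for bypass at most about 87% on the current split). For bands, alternatively state the larger effect on which 60 per arm relies.

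The cost is protocol wording and a less favourable stated subgroup power. No extra patients are needed if the power is restated. Keeping 90% within bypass would instead need more bypass invitations than the current 155.
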